## Abstract

**Background:**

Manual screening of a Kato-Katz (KK) thick stool smear remains the current standard to monitor the impact of large-scale deworming programs against soil-transmitted helminths (STHs). To improve this diagnostic standard, we recently designed an artificial intelligence based digital pathology system (AI-DP) for digital image capture and analysis of KK thick smears. Preliminary results of its diagnostic performance are encouraging, and a comprehensive evaluation of this technology as a cost-efficient end-to-end diagnostic to inform STH control programs against the target product profiles (TPP) of the World Health Organisation (WHO) is the next step for validation.

**Methods:**

Here, we describe the study protocol for a comprehensive evaluation of the AI-DP based on its (i) diagnostic performance, (ii) repeatability/reproducibility, (iii) time-to-result, (iv) cost-efficiency to inform large-scale deworming programs, and (v) usability in both laboratory and field settings. For each of these five attributes, we designed separate experiments with sufficient power to verify the non-inferiority of the AI-DP (KK2.0) over the manual screening of the KK stool thick smears (KK1.0). These experiments will be conducted in two STH endemic countries with national deworming programs (Ethiopia and Uganda), focussing on school-age children only.

**Discussion:**

This comprehensive study will provide the necessary data to make an evidence-based decision on whether the technology is indeed performant and a cost-efficient end-to-end diagnostic to inform large-scale deworming programs against STHs. Following the protocolized collection of high-quality data we will seek approval by WHO. Through the dissemination of our methodology and statistics, we hope to support additional developments in AI-DP technologies for other neglected tropical diseases in resource-limited settings.

**Trial registration:**

The trial was registered on September 29, 2023 Clinicaltrials.gov (ID: NCT06055530).

## Introduction

Soil-transmitted helminths (STHs) are a group of intestinal roundworms transmitted through the uptake of infectious life stages in the environment (often soil, referring to their common name) [1, 2]. STHs, including the giant round worm (*Ascaris lumbricoides*), whipworm (*Trichuris trichiura*) and hookworms (*Necator americanus* and *Ancylostoma duodenale*), primarily affect impoverished communities in (sub)tropical countries [1–3]. It was estimated that 24% of the global population is affected by at least one of these STHs, resulting in a total loss of 1.9 million disability-adjusted life years in 2019 [4, 5]. In response to this public health issue, many STH-endemic countries have implemented national school-based deworming programs, providing periodic oral anthelminthic treatment to the children at the schools in the program [6–8]. The pharmaceutical industry’s contribution of more than 6.5 billion anthelmintic tablets for at-risk populations since 2016 has undoubtedly contributed to reducing the disease burden in various STH-endemic countries [9, 10].

Encouraged by this progress, World Health Organization (WHO) has published its roadmap for STHs for the next decade (2020–2030), encompassing six ambitious targets (**Table 1**) [7, 11]. To advance towards the first two targets, it will be critical to periodically assess the STH infection prevalence, of both any intensity and moderate-to-heavy intensity (MHI) infections. The prevalence of any intensity STH infection is deployed as a parameter to determine the frequency of deworming (**Target #2**), while the elimination as a public health problem is defined when prevalence of MHI infections is less than 2% (**Target #1**) [7].

**Table 1 pone.0309816.t001:** The six 2030 targets and corresponding milestones put forward by the WHO [7].

Target		Milestone
#1	Achieve and maintain elimination of STH morbidity in pre-school-aged and school-aged children	98 countries with <2% children with MHI infections
#2	Reduce the number of tablets needed for large-scale deworming programs for STHs	50% reduction
#3	Increase domestic financial support to deworm STHs	25 countries deworming children by domestic funds
#4	Establish an efficient STH control program in adolescent, pregnant and lactating women of reproductive age	Coverage equals 75%
#5	Establish an efficient strongyloidiasis control program in school-aged children	75% of the children at risk of *Strongyloides* receiving ivermectin
#6	Ensure universal access to at least basic sanitation and hygiene by 2030 in STH-endemic areas	Reduce open defecation to 0%

Microscopic examination of a stool smear using the Kato-Katz (KK) thick smear technique and manual counting of STH eggs remain the recommended diagnostic standard for epidemiological surveys designed to inform large-scale deworming programs [7, 12, 13]. While KK thick smear is the sole diagnostic method mentioned in the 2030 targets for STHs [7], this diagnostic tool has some significant pitfalls: test results are prone to human error; it lacks clinical sensitivity when the intensity of infections is low, and hookworm eggs disappear when smears are not examined within 1h following preparation of the smear [14–17]. Within the last two decades, a variety of alternative diagnostic tools have been developed or repurposed, and subsequently evaluated for the diagnosis of STH infections in children [13, 18–21]. Despite improved clinical sensitivity for some diagnostic tools [15, 16], their integration into national deworming programs has been challenging due to labour-intensive procedures and resource demands [22]. Furthermore, as programs progress toward STH control and elimination, clinical specificity becomes increasingly more important [23]. Indeed, in the WHO’s target product profiles (TPPs) for new diagnostic tools to monitor large-scale deworming programs against STHs, the clinical sensitivity can drop to 60%, while the clinical specificity should be at least 94% [24]. The high clinical specificity of KK thick smear (≥95) [16, 25, 26] remains a strong advantage, reinforcing its likely role as a reference diagnostic for the next decade. While KK thick smear is likely to remain crucial, ongoing research and innovations in diagnostic technology show promise to address its limitations and contribute to more effective STH monitoring and control strategies [27, 28].

A clear opportunity lies in the automation of egg counting, the step which is most prone to human error, laborious and time-demanding (egg counting takes 80% of the time-to-result, including data entry) [22]. We prototyped a proof-of-concept artificial intelligence-based digital pathology (AI-DP) device and demonstrated it for automated scanning and detection of STH eggs in KK thick smears [27]. Today, this AI-DP offers (i) electronic data capturing (EDC), (ii) whole slide imaging (WSI), (iii) an AI model and according AI development pipeline, (iv) AI results verification, and (v) a cloud-based reporting and monitoring dashboard that can be integrated into existing health systems while minimizing data entry / sharing errors (see also **Fig 1**).

**Fig 1 pone.0309816.g001:**
[figure not shown]
An overview of how Kato-Katz (KK) thick smears are processed with the AI-DP (KK2.0). AI: artificial intelligence, KK: Kato-Katz. Figure created using BioRender.com.

Preliminary results highlight the promising performance of the AI-DP method for quantifying STHs [Cure-Bolt under review]. The study showed higher detection rates for *Ascaris* and comparable rates for *Trichuris* and hookworms compared to the manual KK thick smear (KK1.0). Specifically, at the 30-minute mark, our AI-DP based on KK thick smears (KK2.0) identified 49.8% of *Ascaris* cases *vs*. 37.6% by KK1.0, with slight variations observed at 24 hours. Although the mean fecal egg counts (expressed in eggs per gram of stool (EPG)) were generally similar, KK2.0 uniquely identified an additional 10% of low intensity infections for *Ascari*. These findings suggest that our KK2.0 prototype holds substantial potential for reliable STH diagnosis and the development of automated digital microscopes following WHO guidelines. Considering the encouraging results and field tests, a comprehensive prospective, WHO-TPP aligned, in- field evaluation of the AI-DP is urgently needed to provide the necessary data for health decision makers to make an evidence-based decision on whether this technology can be recommended to inform large-scale deworming programs against STHs.

Here, we describe the study protocol for a comprehensive evaluation of an AI-DP based on its (i) diagnostic performance, (ii) repeatability/reproducibility, (iii) time-to-result, (iv) cost-efficiency to inform large-scale deworming programs, and (v) usability both in a laboratory and field setting. For each of these five attributes, separate experiments were designed to test the hypothesis that the AI-DP (KK2.0) is non-inferior when compared to the manual screening of the KK smears (KK1.0). The field work will be conducted in two STH endemic countries with a national deworming program (Ethiopia and Uganda), focussing on school-age children (SAC) only. Through the dissemination of our methodology and statistics, we also hope to support additional developments in any AI-DP technologies for other neglected tropical diseases in resource-limited settings.

## Methods

This protocol is being reported using the SPIRIT (Standard Protocol Items: Recommendations for Interventional Trials) framework and checklists (**S1 File**). **Fig 2** presents a tentative schedule of the study.

**Fig 2 pone.0309816.g002:**
[figure not shown]
Tentative schedule for enrolment and assessments. AI-DP: artificial intelligence based digital pathology system.

### 1 Ethics statement

This study protocol and the informed consent documents (**S2 File**) were approved by the institutional review board of the Faculty of Medicine and Health Sciences of Ghent University (Belgium) (ONZ-2023-0496; September 29, 2023). Approval by the institutional review board Health Institute of Jimma University (Ethiopia) (JUIH/IRB/621/23; 13/10/2023), the Vector Control Division Research Ethics committee (Uganda) (VCDR-2023-24; 08/11/2023). Parent(s)/guardian(s) of the participants will sign an informed consent document (**S2 File**) indicating that they understand both the purpose, and the procedures required for the study, and that they are willing to have their child participate in the study. If the child is ≥6 years old, he/she will have to orally assent to participate in the study. Participants ≥8 years old (≥12 years old in Ethiopia) will only be included if they sign an assent form (**S2 File**) indicating that they understood both the purpose of the study and the procedures required for the study, and they are willing to participate in the study. Every child that tests positive on KK1.0 or whose stool sample undergoes the egg spiking procedure will receive a single oral dose of 400 mg albendazole or 500 mg mebendazole in case of STH infections, and 40 mg/kg body weight praziquantel in case of *Schistosoma mansoni* infections. If the presence of eggs other than STHs and *S*. *mansoni* is confirmed, children will be referred to the nearest health centre.

The use of collected data will be strictly limited to the research objectives outlined in this study, and to enhance the accuracy and reliability of the AI diagnostic tool in identifying and diagnosing STHs. The study will adhere to the highest ethical standards, ensuring participant privacy and data protection. All data will be treated with strict confidentiality, and measures will be implemented to anonymize the data to ensure participant anonymity.

### 2 Study population and study sites

The study will focus on SAC (age 5–14) only, since they are the major target of large-scale deworming programs against STHs [6]. We will apply the inclusion and exclusion criteria summarized in **Table 2**. These criteria have been adapted from criteria standardized and applied throughout a series of drug efficacy trials [29].

**Table 2 pone.0309816.t002:** Inclusion and exclusion criteria that will be endorsed during the recruitment of participants (adapted from [29]).

Inclusion criteria	Exclusion criteria
• Subject, male or female, is 5–14 years of age • Parent(s)/guardian(s) of subject signed an informed consent document indicating that they understand the purpose and procedures required for the study and that they are willing to have their child participate in the study • Subject of ≥5 years old has orally assented to participate in the study • Subject of ≥6 (Uganda) / ≥12 (Ethiopia) years old has signed an assent form indicating that they understand the purpose of the study and procedures required for the study, and are willing to participate in the study* • Subject has provided a stool sample of minimum 5 grams	• Subject has active diarrhoea (defined as the passage of 3 or more loose or liquid stools per day) • Subject is experiencing a severe concurrent medical condition or has an acute medical condition • Subject has received anthelmintic treatment within 90 days prior to the start of the study

*These differences in inclusion criteria are due to differences in national policies.

The study will be conducted in both Ethiopia and Uganda. The selection of these countries and the corresponding partners (Ethiopia: Jimma University; Uganda: Vector Control and Neglected Tropical Diseases Division, Ministry of Health of Uganda) were based on ongoing collaborations [20, 29–36], the presence of an STH control program (Ethiopia: since 2015; Uganda: since 2003), and the availability of recent data on both the prevalence and intensity of STH infections [31, 32, 37]. Finally, both countries operate differently, allowing AI-DP evaluation in a fully equipped laboratory (Jimma University, Ethiopia) and a field setting (VCD, Uganda) that best mimic monitoring and evaluation (M&E) activities as part of the national STH deworming program. In Ethiopia, the study will be conducted in Jimma Zone, Oromia Regional state. In Uganda, the study will be conducted in the district of Central Uganda. The schools will be selected based on previously available data, to ensure sufficient STH cases.

### 3 Processing KK thick smears with our AI-DP (KK2.0)

Processing KK thick smears with the AI-DP (KK2.0) is graphically illustrated in **Fig 1**. To facilitate study management, the AI-DP enables EDC for registering study participants (**step 1**) and provides QR printing spreadsheets and QR label templates. Once the KK thick smears are prepared (with QR code on the slide) (**step 2**), the scanning process is initiated (**step 3**). This involves manually loading of the smears into the scanner using a specialized slide holder, after which the QR code is read, and boundary of the stool smear is determined. If required, the user is prompted to manually adjust the scan boundary. In a next step, the slide is automatically scanned, and the scanner captures focus stacks, saving eight images at every field-of-view (FOV) within the KK thick smear (**step 3**). Following slide scanning, images are transferred to the Slide Manager, and FOVs are analyzed by the AI model for the detection, classification, and quantification of helminth eggs (**step 4**). In a final step, the results generated by the AI undergo review and verification (**step 5**). This is done through the EggInspector tool, presenting all the AI-determinants from a slide to a trained verifier.

### 4 The experiments to comprehensively evaluate KK2.0

This comprehensive evaluation consists of five experiments, each one designed to evaluate one of the five attributes: (i) diagnostic performance, (ii) repeatability/reproducibility, (iii) time-to-result, (iv) cost-efficiency to inform large-scale deworming programs, and (v) usability in both a laboratory and field setting. **Table 3** provides an overview of the hypotheses, the primary and secondary outcomes for each experiment separately. Across these five experiments, we defined nine hypotheses, 13 primary and 17 secondary outcomes. Generally, we hypothesize that KK2.0 is non-inferior to KK1.0. Note that a hypothesis was not defined for both the time-to-result and usability experiments. This was because the outcomes of the time-to-result experiment will feed into the experiment on cost-efficiency and because the usability experiment was designed to gain insights into how we can further improve the usability of KK2.0 only. In the following sections we will discuss each experiment in detail. The sample size calculation and the statistical data analysis will be discussed in **section 5**.

**Table 3 pone.0309816.t003:** An overview of the hypotheses, primary, and secondary outcomes to comprehensively evaluate KK2.0.

Experiment	Hypotheses			Primary outcomes		Secondary outcomes
1) Diagnostic performance	**H1.1**	the clinical sensitivity of KK2.0 to detect low intensity infections is non-inferior to that of KK1.0 for *Ascaris*, *Trichuris* and hookworms	**P1.1**	the clinical sensitivity of KK2.0 and KK1.0 to detect low intensity infections of *Ascaris*, *Trichuris* and hookworms	**S1.1**	the clinical sensitivity and clinical specificity of KK1.0 and KK2.0 to detect *S*. *mansoni* infections
	**H1.2**	the clinical sensitivity of KK2.0 to detect MHI infections is non-inferior to that of KK1.0 for *Ascaris*, *Trichuris* and hookworms	**P1.2**	the clinical sensitivity of KK2.0 and KK1.0 to detect MHI infections of *Ascaris*, *Trichuris* and hookworms	**S1.2**	the detection limit (the lowest number of eggs that yields a positive test result in 95% of the cases) for both KK1.0 and KK2.0, and *Ascaris*, *Trichuris*, hookworm, and *S*. *mansoni* separately
	**H1.3**	the clinical specificity of KK2.0 to detect any intensity infections is non-inferior to that of KK1.0 for *Ascaris*, *Trichuris* and hookworms	**P1.3**	the clinical specificity of KK2.0 and KK1.0 to detect any intensity infections of *Ascaris*, *Trichuris* and hookworms	**S1.3**	the egg recovery rate of KK1.0 and KK2.0 when compared to the ground truth for *Ascaris*, *Trichuris*, hookworms and *S*. *mansoni*
	**H1.4**	the clinical specificity of KK2.0 to detect MHI infections is non-inferior to that of KK1.0 for *Ascaris*, *Trichuris* and hookworms	**P1.4**	the clinical specificity of KK2.0 and KK1.0 to detect MHI infections of *Ascaris*, *Trichuris* and hookworms	**S1.4**	the clinical sensitivity and clinical specificity of the AI-DP when the AI verification process is simplified (limited selection of AI objects presented for verification) or even omitted
2) Repeatability and reproducibility	**H2.1**	the repeatability and the reproducibility of the scanning process is at least 99%	**P2.1**	the repeatability and the reproducibility of the scanning process	**S2.1**	the agreement between repeated egg counts for *Ascaris*, *Trichuris* and *S*. *mansoni*
	**H2.2**	the repeatability and the reproducibility of AI verification process is at least 99%	**P2.2**	the repeatability and the reproducibility of the AI verification process	**S2.2**	the repeatability and reproducibility in test results when the AI verification process is simplified (limited selection of AI objects presented for verification) or even omitted
	**H2.3**	the repeatability and the reproducibility of KK2.0 is at least 99%	**P2.3**	the repeatability and the reproducibility of the KK2.0	**S2.3**	the repeatability and the reproducibility of KK1.0
3) Time-to-result		We did not define any hypotheses, as the outcomes of this experiment will feed into the experiment on cost-efficiency (**section 4.4**)	**P3.1**	time-to-result for KK2.0	**S3.1**	time for participant registration using EDC tools and QR printing
					**S3.2**	the correlation between time-to-result and *Ascaris*, *Trichuris* and *S*. *mansoni* egg counts recorded by KK2.0
					**S3.3**	time-to-result of the AI-DP when the AI verification process is simplified (limited selection of AI objects presented for verification) or even omitted
4) Cost-efficiency	**H4.1**	the cost-efficiency of KK2.0 to make a reliable program stopping decision is non-inferior to that of KK1.0	**P4.1**	the total survey cost to reliably inform a stop decision the program for KK2.0 and KK1.0	**S4.1**	the total survey cost to make reliable program decisions on the frequency of large-scale deworming programs for KK2.0 and KK1.0
	**H4.2**	the cost-efficiency of KK2.0 to reliably declare that STHs are eliminated as a public health problem is non-inferior to that of KK1.0	**P4.2**	the total survey cost to reliably inform a declaration that STH are eliminated as a public health problem for KK2.0 and KK1.0	**S4.2**	the total survey cost to reliably monitor the therapeutic drug efficacy of anthelmintic against STHs for KK2.0
					**S4.3**	the total survey cost to make reliable program decisions on the frequency of large-scale deworming programs for KK2.0 when the AI verification process is simplified (limited selection of AI objects presented for verification) or even omitted
					**S4.4**	the required performance of AI to make reliable program decisions on the frequency of large-scale deworming programs for KK2.0
					**S4.5**	the optimal set-up for KK2.0 (sample throughput; number of AI-DP devices; number of operators) to inform large-scale deworming programs when deployed in a fully equipped laboratory and M&E setting
5) Usability		For this experiment, we did not define any hypotheses	**P5.1**	ease-of-use/ease-of-learning of (i) the training (ii) the setup, (iii) the scanning, and (iv) the AI verification process for the identified end-users	**S5.1**	identification of other barriers/facilitators for (i) the training (ii) the setup, (iii) the scanning, and (iv) the AI verification process by the identified end-users
			**P5.2**	efficiency of (i) the training (ii) the setup, (iii) the scanning, and (iv) the AI verification process for the identified end-users	**S5.2**	other comparative metrics such as task completion time and rates, error rates, and success rates
			**P5.3**	satisfaction/low user burden of (i) the training (ii) the setup, (iii) the scanning, and (iv) the AI verification process for the identified end-users		

#### 4.1 Diagnostic performance

**Fig 3** provides an overview of the proposed study design for the experiment on the diagnostic performance. Generally, this experiment consists of five consecutive steps, with the second step offering two methods to validate diagnostic performance. The first method involves verifying egg counts by reviewing and counting all eggs within the captured FOVs. The second method entails spiking a minimum number of eggs into randomly selected stool samples to achieve counts indicating an MHI infection. In the **first step** of the experiment, fresh stool samples will be collected from SAC at the schools. In the **second step**, the consistency of the stool samples will be scored based on the Bristol Stool Chart [38]. Subsequently, sample will be homogenised, and one KK thick smear per sample will be prepared in one of the two following ways for the two validation methods described above. For FOV-based validation (**step 2A**), samples will be processed as recommended by WHO. For egg spiking-based validation (**step 2B**), the cone of stool (after removing the KK template) will be spiked with purified eggs to artificially increase the egg counts to at least an MHI infection (*Ascaris*: >209 eggs; *Trichuris*: >42 eggs; hookworms: >84 eggs). This step 2B will only be done in a subset of the samples (never on samples that are processed through 2A) and is introduced to ensure that sufficient cases of MHI infections for each of the STHs are obtained (see also **section 5**). The selection of the samples to be spiked will be done through a randomization process. In the **third step** and following a smear clearing time of 30 min, the smears will be randomly allocated to be analysed by either KK1.0 (even participant ID) or KK2.0 (odd participant IDs). This randomization process is required to avoid systematic bias due to hookworm egg degradation over time [13, 14, 39]. In the **fourth step**, egg counts will be recorded for each helminth species (*Ascaris*, *Trichuris*, hookworm and *S*. *mansoni*), separately. Thereafter (**step 5**), KK thick smears will be stored at 4°C to be used in the context of the experiment on reproducibility/repeatability (see **section 4.2**). In Ethiopia, sample processing (from step 2 onwards) will be conducted in the Neglected Tropical Disease Laboratory of Jimma University (a fully equipped laboratory setting), while in Uganda all steps will be conducted on-site (M&E setting).

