**Fig 3 pone.0309816.g003:**
[figure not shown]
Overview of the study design for the experiment on diagnostic performance. FOV: field-of-view, KK: Kato-Katz. Figure created using BioRender.com.

In absence of a gold standard, it will be important to define the ground truth for each slide separately, to test the hypotheses (H1.1 – H.1.4). For the slides that were not spiked, all FOVs that were captured through the AI-DP will be manually annotated by one trained laboratory technician. A second trained laboratory technician will then verify the annotations. In case of disagreement, a third trained laboratory technician will make the final call. For the spiked samples, the ground truth (samples being classified as MHI infection) is already established through the process of spiking.

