### 6 Statistical data analysis

#### 6.1 Diagnostic performance

*6*.*1*.*1 Primary outcomes*. We will draw contingency tables representing the test results of both KK1.0 and KK2.0 for each type of ground truth (no, low intensity and MHI infections) and STH species (*Ascaris*, *Trichuris* and hookworms). From these tables, both the clinical sensitivity and specificity, and the corresponding 95% CI (Wald) will be calculated for each test and STH separately. Subsequently, we will also calculate the 90% CI around the difference in performance (KK2.0-KK1.0) accounting for multiple hypotheses testing. Given that test results are paired (same smears are processed by KK1.0 and KK2.0, we will use the formulae described by Newcombe for paired data [46]. We will conclude that the clinical sensitivity or specificity of KK2.0 for a particular STH is non-inferior if the lower limit of the adjusted 90% CI does not include the -5-point percent.

*6*.*1*.*2 Secondary outcomes*. We will draw contingency tables representing the test results of both KK1.0 and KK2.0 for each type of ground truth for *S*. *mansoni* infections. From these tables, both the clinical sensitivity and specificity, and the corresponding 95% CI will be calculated (***S1*.*1***).

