### Estimates of diagnostic performance are not absolute, but relative to KK1.0

For many infectious diseases, the absence of a gold standard (100% sensitivity and specificity) is a universal challenge to estimate the true performance of new diagnostics [47, 48]. To overcome this obstacle for STHs, it has been suggested to examine more stool samples with multiple diagnostic methods [49–52], and to deploy statistical methodologies that account for the absence of a gold standard [48]. In our study, we will determine the diagnostic performance of the AI-DP relative to the current diagnostic standard (KK1.0). In our opinion choosing KK1.0 as a sole comparator is justified. First, the AI-DP aims to improve the current KK1.0, and hence it is the obvious comparator to test the non-inferiority hypotheses. Second, for MHI infections, KK1.0 remains the sole diagnostic method to define the intensity of infections [23, 24]. Third, it has recently been shown that the clinical specificity, rather than the clinical sensitivity, will become more important when programs progress towards control and elimination of STH [23, 53]. Clinical specificity of KK1.0 thick smear (95% [16, 25, 26]) has never been considered as a drawback, which takes away the need for a more sensitive comparator (e.g., qPCR [15, 54]). Finally, we carefully designed the experiments so that we can ensure the true underlying infection status. For the KK smears representing no infections or infections of low intensity, we will have the ground truth based on the scans of the KK thick smears, while for the smears representing MHI infections we will spike the slides with known number of eggs. This design allows us to draw the appropriate conclusions around the defined non-inferiority hypotheses without the need of other diagnostic methods (e.g., qPCR) or more complex statistical models that account for a gold standard.

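### For unspiked hookworm smears, alternating the reading order does not remove degradation bias: the ground truth comes from the KK2.0 scan, so the pooled comparison leans towards KK2.0

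*Protocol article*

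**What the plan says.** **Reading order (section 4.1, third step).** Reading starts "following a smear clearing time of 30 min", and then "the smears will be randomly allocated to be analysed by either KK1.0 (even participant ID) or KK2.0 (odd participant IDs"). The reason given is: "This randomization process is required to avoid systematic bias due to hookworm egg degradation over time".

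**Pairing (section 6.1.1).** The analysis is paired because the "same smears are processed by KK1.0 and KK2.0". One contingency table is drawn per species and ground-truth class, with no split by reading order. Non-inferiority is judged on the difference KK2.0 − KK1.0 against −5 points.

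**Reference, unspiked smears (section 4.1, text after Fig 3).** "all FOVs that were captured through the AI-DP will be manually annotated by one trained laboratory technician", followed by a second technician's check. The Discussion repeats that for smears with no or low-intensity infection "we will have the ground truth based on the scans of the KK thick smears".

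**Reference, spiked smears (same place).** "the ground truth (samples being classified as MHI infection) is already established through the process of spiking".

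**Egg loss (Introduction).** "hookworm eggs disappear when smears are not examined within 1h following preparation of the smear".

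**The concern.** Alternating the order cancels a time effect only if the reference does not itself move with the order. For unspiked smears it does move, because it is fixed at the moment of the AI-DP scan.

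- **KK2.0 first.** The reference and KK2.0 see the early smear. Eggs lost before the KK1.0 reading become KK1.0 false negatives.
- **KK1.0 first.** The reference and KK2.0 see the late smear. Where all eggs have gone by then, a correct KK1.0 positive is scored as a false positive.

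At stake are the hookworm conclusions on sensitivity for low-intensity infection (H1.1) and on specificity for any infection (H1.3). A bias towards the new test shifts the confidence interval away from −5 points, so it makes a wrong claim of non-inferiority more likely. The article tells readers that this source of bias has been dealt with.

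**Working it through.** **1. Timing, side by side (unspiked smears).**

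| Order | Reference sees | KK2.0 sees | KK1.0 sees |
|---|---|---|---|
| KK2.0 first | early smear | early smear | late smear |
| KK1.0 first | late smear | late smear | early smear |

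**2. The plan's own figures.** No stated figure is disputed. The 140 low-intensity hookworm smears (H1.1) and 225 uninfected smears (H1.3) come from simulations in S3 File, which is not shown. As a plausibility check, take n = (z₁₋α + z₀.₈₀)² × discordance / 0.05², with one-sided α = 0.05/3. The multipliers are 2.128 + 0.842 = 2.970. Then n = 225 needs discordance 225 × 0.0025 / 8.82 = 0.064. That would arise, for example, with specificity 0.95 and correlation 0.33: 2 × 0.95 × 0.05 × 0.67 = 0.064. So 225 is attainable but cannot be verified.

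**3. Why the net has one sign.** Assume two equally good readers, n eggs at the early time, detection probability d per visible egg, and survival s per egg between readings. Let

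- P = 1 − (1 − d)ⁿ (positive on the early smear),
- Q = 1 − (1 − ds)ⁿ (positive on the late smear),
- T = 1 − (1 − s)ⁿ (at least one egg left at the late time).

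Sensitivity difference, KK2.0 − KK1.0:

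- KK2.0 first: P − Q, which favours KK2.0.
- KK1.0 first: Q/T − P, which favours KK1.0, because reference-positive smears held more eggs when KK1.0 read them.
- Pooled, orders 50:50: [(P + Q) − (Q + TP)] / (1 + T) = P(1 − T)/(1 + T).

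The pooled value is positive whenever some smears lose all their eggs, and zero only if none do.

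Example with n = 2, d = 0.9, s = 0.7: P = 1 − 0.1² = 0.990; Q = 1 − 0.37² = 0.863; T = 1 − 0.3² = 0.910.

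- KK2.0 first: 0.990 − 0.863 = +12.7 points.
- KK1.0 first: 0.863/0.910 − 0.990 = −4.2 points.
- Pooled: 0.990 × 0.09/1.91 = +4.7 points.
- In the KK1.0-first order, 0.09 × 0.99 = 8.9% of these infected smears become KK1.0 false positives.

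**4. Range over egg counts.** The inputs are all assumptions: negative binomial counts with mean 2, 5 or 10; d = 0.7 or 0.9; 40% of children exposed; orders 50:50. Pooled bias in percentage points:

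| Egg survival between readings | Sensitivity (H1.1) | Specificity (H1.3) |
|---|---|---|
| 90% | +0.6 to +1.6 | +0.2 to +0.4 |
| 70% | +2.2 to +5.8 | +0.7 to +1.5 |
| 50% | +4.9 to +12.6 | +1.6 to +3.0 |

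By order at 70% survival:

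- Sensitivity: +6 to +12 points with KK2.0 first, and −0.7 to −4.1 with KK1.0 first.
- Specificity: unaffected with KK2.0 first, and +1.5 to +3.0 points with KK1.0 first.

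**5. Two controls.** If the reference is the eggs present at the first reading, whichever method makes it, the pooled bias is zero within simulation error (at most about 0.2 points). If the truth is fixed before both readings, as with spiking, the pooled bias is again about zero. The scan-timed reference is therefore the cause.

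**6. Effect on the error rate.** Planned precision implies a standard error of 5/2.970 = 1.684 points. If KK2.0 is truly 5 points worse, the chance of declaring non-inferiority under a bias of b points is Φ(b/1.684 − 2.128). This is 1.7% at b = 0, and about 6%, 17% and 60% at b = 1, 2 and 4 (normal approximation).

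**The case against.** **The size is not known, and may be small.** This stands. The article gives no decay rate and no gap between readings. Reading starts 30 minutes after preparation and the Introduction places the loss at 1 hour, so prompt second readings could leave little bias. At 90% survival the sensitivity bias is at most 1.6 points, and specificity bias stays below the margin in every scenario run. A reader might infer that hookworm non-inferiority will follow from timing alone. The documents do not support that, because it needs a large assumed loss.

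**The reference is not always scan-based.** This also stands. A reader might extend the point to all smears, but for spiked smears the truth is set before either reading and alternation works there.

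**The error does not run against KK1.0 on every measure in both orders.** Correct. With KK1.0 first, the sensitivity contrast leans against KK2.0 and offsets part of the bias. The offset is incomplete, and the pooled result still favours KK2.0.

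**Section 6.1.2 refers to ground truth at the first examination.** It does so only for the detection limit (S1.2). When KK1.0 reads first, no scan from that moment exists to annotate.

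**Making order-selected contrasts primary would do harm.** Agreed. KK1.0-first sensitivity alone is biased against KK2.0 by up to 4.1 points at 70% survival. Half the smears also gives power of only Φ(2.970/√2 − 2.128), about 49%.

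**Conclusion.** The stated property fails for unspiked hookworm smears. Alternation equalises when each method reads but leaves the reference tied to KK2.0, and pooling the orders does not undo this. Hookworm H1.1 and H1.3 carry a net bias towards KK2.0 whenever some smears lose all visible eggs between readings.

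The direction follows from the design, given readers of equal ability who detect eggs independently. The size rests on assumed survival, detection and egg counts. It runs from negligible to beyond the 5-point margin for sensitivity, and stays below the margin for specificity. The point is confined to one species and to unspiked smears. It limits what may be concluded and does not invalidate the experiment.

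**What to change.** 1. In section 4.1, withdraw the statement that alternation avoids degradation bias for unspiked hookworm smears. Say that ID parity decides which method reads first.
2. Record the time of each reading, and hence the interval between them, for every smear.
3. In section 6.1.1, keep the pooled hookworm analysis and pre-specify the H1.1 and H1.3 contrasts by reading order beside it. KK2.0-first specificity is free of timing bias. For sensitivity, KK1.0-first is the conservative bound and KK2.0-first the favourable one.
4. Claim hookworm non-inferiority without qualification only if the order-specific estimates are consistent with the pooled result. Define consistent before the data are analysed. Otherwise state the claim with the order-specific results and the recorded intervals.

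The cost is one extra recorded time per reading and some added analysis. No extra smears are needed. Each order group holds about half the smears, with about 49% power alone at the minimum sample sizes. The order-specific results should therefore serve as a check on bias and a limit on the claim, not as replacement primary tests.
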